### Interim analyses {21b}

An interim analysis is not planned. The investigators will closely monitor the general safety of the trial participants.

### Methods for additional analyses (e.g., subgroup analyses) {20b}

In case of significant differences, comparisons between the placebo and Neu2000K low-dose groups, and placebo and Neu2000K high-dose groups will be conducted. For secondary endpoint analyses, Student’s *t*-test, Mann–Whitney’s *U*-test, chi-square test, Fisher’s exact test, and Cochran-Mantel–Haenszel shift test according to the type of variable will be used to compare the treatment groups. Secondary endpoints for statistical tests will be performed under a two-sided 5% significance level. Adjustment for multiple tests is not considered.

### Methods in analysis to handle protocol non-adherence and any statistical methods to handle missing data {20c}

Due to the extremely high early mortality of OHCA, the per-protocol analysis will consist of patients who received more than 80% of the planned study drug administration (5 or 6 infusions of the study drug or placebo). Any alternative method for missing values will not be used.

### Plans to give access to the full protocol, participant-level data, and statistical code {31c}

The study protocol, statistical code, and data can be supplied on a reasonable request and with approval from relevant authorities. Patient-level data can only be requested after full publication.

## Oversight and monitoring

### Composition of the coordinating center and trial steering committee {5d}

The investigators and sponsors supervise the AWAKE trial, which is a sponsor-initiated multi-center study. The steering committee includes investigators in each participating site, sponsor, and Clinical Research Organization (CRO).

### Composition of the data monitoring committee, its role, and reporting structure {21a}

Medical Excellence, a professional contract research organization, will monitor the study data, trial enrollment, and conduct. The data will be stored in a secure case report system. Hence, the size of this study is limited, no data monitoring committee will be formed. Safety reports will be filed to the local ethical committee and the Ministry of Food and Drug Safety of Korea.

### Adverse event reporting and harms {22}

Adverse events (AE) will be assessed daily for the first 5 days, and adverse events occurring after day 7 will be evaluated during follow-up on day 14 and day 90. At each assessment of adverse events, serious adverse events (SAE) and suspected unexpected serious adverse reactions (SUSAR) should be recorded in AE form by the investigator and evaluated. Record of each SAE and SUSAR requires the following variables: description of the event, onset and end of the event, severity, relation to the intervention, action taken, and outcome. Any adverse events occurring during the study will be treated according to the established standards, and the subject will be followed until the event has disappeared or stabilized. On a yearly basis, a safety report containing information on SAE and SUSAR will be submitted to the Ministry of Food and Drug Safety of Korea. For each AE, the investigator assesses potential causality between investigational products, and whether the reaction is suspected will be assessed by the sponsor. An SAE will be defined as any AE that results in death, is life-threatening, requires prolongation of hospitalization, or results in significant disability, including congenital anomaly or birth defect. The sponsor will be responsible to report all life-threatening lethal SUSARS to the Ministry of Food and Drug Safety of Korea as soon as possible and no later than 7 days after the event, and non-life-threatening SUSARs no later than 15 days after the event.

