### Criteria for discontinuing or modifying allocated interventions {11b}

The subject or the subject’s next of kin has the right to withdraw from the study at any time for any reason without prejudice to his or her future medical care. Any subject who withdraws consent to participate in the study will be removed immediately from the further treatment and/or study observation.

The investigator and the sponsor have the right to withdraw a subject from the study if any of the following occurs: unexpected significant intercurrent illness, refusal to continue clinical observations, or decision by the investigator that study termination is the best medical interest of the subject.

Unless specific request by the subject, the subject will be followed for the primary endpoint until the end of the study period. When a subject or legally acceptable representative request withdrawal of the study, the end of study case report form will be completed with an explanation for the withdrawal as well as a complete final evaluation and assessments. If the withdrawal of a subject is due to an adverse event, follow-up visits should be scheduled until the adverse event has been resolved or stabilized. Unless consent has been withdrawn, follow-up data on deaths and hospitalizations will be collected until study termination since the enrollment of the subject.

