### Outcomes {12}

The primary endpoint is biomarker of cerebral injury assessed by blood NSE level on the 3rd day.

The secondary endpoints include the following: biomarkers of cerebral injury assessed by NSE on the 4th day, difference in blood NSE on the 1st and 3rd day, difference in blood NSE on the 4th and 5th day, and blood S100beta on the 4th day. Imaging marker of cerebral injury is assessed by brain MRI apparent diffusion coefficient (ADC) images on the 4th or 5th day. Clinical and functional markers of cerebral injury are assessed by cerebral performance category (CPC) and Modified Rankin Scale (mRS) on the 5th day, day 14, or at discharge within days 14 and 90. Safety is assessed by any adverse event during the study period.

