### Plans to promote participant retention and complete follow-up {18b}

The majority of patients are expected to remain in the intensive care unit during the initial 3 days and hospitalized at least 5 days, where most data collection and all biomarker sampling are scheduled. The contact information for patients and their next of kin is stored with the intention of inviting patients to the functional assessment at day 14 and day 90.

If the patient cannot visit the hospital, a follow-up questionnaire by letter, phone, or electrical message would be used for communication.

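### Adverse events starting on day 6 or 7 have no stated collection point, contrary to the safety endpoint, and a new admission is not in itself a seriousness criterion

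*Protocol article*

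**What the plan says.** All references are to the protocol article.

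- **Scope of the safety endpoint**, Outcomes {12}: "Safety is assessed by any adverse event during the study period".
- **First collection rule**, Adverse event reporting and harms {22}: "Adverse events (AE) will be assessed daily for the first 5 days".
- **Second collection rule**, same sentence: "adverse events occurring after day 7 will be evaluated during follow-up on day 14 and day 90". The next sentence ties the recording of serious events and suspected unexpected serious reactions to each of these assessments.
- **Seriousness**, same section: "An SAE will be defined as any AE that results in death, is life-threatening, requires prolongation of hospitalization, or results in significant disability". Congenital anomaly and birth defect are placed under disability.
- **Hospital admissions**, Criteria for discontinuing or modifying allocated interventions {11b}: unless consent is withdrawn, "follow-up data on deaths and hospitalizations will be collected until study termination since the enrollment of the subject".
- **Follow-up**, Plans to promote participant retention and complete follow-up {18b}: most patients are expected to be "hospitalized at least 5 days, where most data collection and all biomarker sampling are scheduled". Contact details are kept with a view to "inviting patients to the functional assessment at day 14 and day 90".

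**The concern.** The endpoint covers the whole study, while the schedule that feeds it names two windows that do not meet. A site that follows the schedule literally has no instruction for an event that begins on day 6 or 7. Because serious events are recorded at the adverse event assessments, a non-fatal serious event starting on those days also lacks a stated recording point.

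The second issue is classification. A patient who has gone home cannot have a prolonged stay. An event that leads to readmission, and is not fatal, life-threatening or disabling, would not enter the serious-event record or the yearly safety report to the Ministry.

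Safety is the trial's second objective. The article plans no interim analysis and no data monitoring committee, so the completeness and classification of the event records matter more than they would under independent oversight.

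**Working it through.** The article gives no figure to reproduce. The check compares the days covered by the two rules with the study period, then reads the seriousness criteria one by one.

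**Inputs**

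- Window 1: daily for five days (section {22}).
- Window 2: onset after day 7, evaluated at days 14 and 90 (section {22}).
- Study period: taken to end at the last stated contact, day 90 (sections {22} and {18b}).
- Dosing: six infusions 12 h apart (Intervention description {11a}).

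**Windows**

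1. Counting from day 1, window 1 is days 1–5 (5 days) and window 2 is days 8–90 (90 − 7 = 83 days). Uncovered: 90 − 5 − 83 = 2 days, namely days 6 and 7.
2. Counting from day 0, with five daily assessments on days 0–4, the total is 91 days. Uncovered: 91 − 5 − 83 = 3 days, namely days 5, 6 and 7.
3. If the second rule is read generously, to include day 7 itself, day 6 is still uncovered when counting from day 1.

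No numbering convention closes the gap.

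**Position relative to dosing**

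The last infusion starts 5 × 12 = 60 h after the first. Daily assessment therefore covers dosing and roughly the next two days. The uncovered days come after that.

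**What else could catch a day 6–7 event**

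- Section {11b} catches deaths and hospitalizations, but not other adverse events.
- Section {22} also says that adverse events in the study are treated and followed to resolution or stability. That governs handling once an event is known; it sets no collection point.
- The sponsor's 7-day and 15-day reporting limits apply whatever the window, but they presuppose that the event has been recorded.

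**Seriousness criteria**

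| Criterion | Listed in {22} |
|---|---|
| Death | yes |
| Life-threatening | yes |
| Prolonged hospital stay | yes |
| New hospital admission | no |
| Significant disability, including congenital anomaly or birth defect | yes |

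Discharge before day 90 is foreseen: section {18b} expects a stay of at least 5 days and provides for contact by letter or phone if the patient cannot come to the hospital. Section {11b} collects the readmission but does not make it a serious event.

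**The case against.** The strongest reply is that full capture was intended. Outcomes {12} sets the scope without exception, and section {22} nowhere says that events on days 6–7 are to be left out. On this view the sentence contains a slip. That is probably right, and a reader should not infer a decision to leave two days uncollected. But the slip sits in the operative collection rule, and sites could apply it in different ways.

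A second reply is that the article condenses protocol version 1.3, which is not shown and may hold the full visit schedule and the complete seriousness definition. This has some force for the seriousness list, which may simply have been shortened. It has less for the windows, because both day limits are stated and they conflict with the endpoint.

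Three stronger readings are tempting, and the document does not support them:

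- **That a countable number of patients lose an event.** One could assume that 10–20% have an onset on days 6–7 and obtain 150 × 0.10 = 15 to 150 × 0.20 = 30 patients. The article gives no incidence. The calculation also supposes that nothing is captured and that all 150 patients are still under observation, although the article itself cites very high early mortality and allows for 28% dropout.
- **That these records are the only safety evidence.** Deaths and hospitalizations are collected separately, the investigators monitor general safety, and the contract research organization monitors the data.
- **That readmissions go uncounted.** They are collected under {11b}, and an event after day 7 is also evaluated at day 14 or day 90. What is lost is the serious classification on the ground of admission alone.

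**Conclusion.** The point stands as an internal inconsistency that is wrong as written. Section {22} leaves two days (three if days are counted from 0) without a stated collection point, against a safety endpoint that covers the whole study. That is 2/7 = 29% of the first week, or 2/90 = about 2% of follow-up to day 90. These percentages describe the schedule and say nothing about how many events are missed, which cannot be estimated from the document.

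The omission of new admission from the seriousness criteria is secondary. It affects classification and reporting, not whether the admission is recorded.

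The conclusion assumes that sites work to the wording shown and that version 1.3 does not already close the gaps. The primary endpoint, alpha and power are unaffected.

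**What to change.** 1. In section {22}, make the windows contiguous by changing *after day 7* to *after day 5*, and state that the day-14 visit collects every event with onset since the day-5 assessment. Tying the rule to that assessment removes any doubt about day numbering. Extending daily assessment to day 7 would also close the gap, but adds two days of assessments.
2. Change the seriousness criterion to *requires hospitalization or prolongation of hospitalization*, so that it agrees with the follow-up in {11b}.
3. Check the charts of patients already enrolled (89 of 150 at the date given under Trial status) for unrecorded events with onset on days 6–7. Assess any readmissions collected under {11b} against the revised criterion.
4. Compare both points with protocol version 1.3 first. If it is already complete, the correction is to the article alone and step 3 becomes a confirmation.

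The cost is two wording changes and limited chart review. No visit is added.

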### Frequency and plans for auditing trial conduct {23}

The trial will be externally monitored by the Good Clinical Practice (GCP) unit at Samsung Medical Center and the Clinical Research Associate of Medical Excellence. There will be mandatory monitoring before and after the study and at least once during the study. The GCP will monitor the inclusion and exclusion criteria, consent obtained in all subjects according to legislation, and data included in the eCRF. The principal investigator will be responsible for all data in the eCRFs.

### Plans for communicating important protocol amendments to relevant parties (e.g., trial participants, ethical committees) {25}

Major modifications of protocol and changes to patient information will be implemented after approval from regulating authorities. Any deviations from the protocol will be fully documented using a breach report form.

### Dissemination plans {31a}

When completed, the study results will be submitted for publication in international peer-reviewed journals and presented at international conferences. The major results would be publicly available.

## Discussion

Ischemic neuronal injury is the major cause that limits the neurologically favorable survival of OHCA patients. Despite vast advances in resuscitation medicine, there is no currently approved drug targeting the reduction of ischemic reperfusion brain injury or improving the clinical outcome of OHCA. At present, there are four other trials enrolling OHCA patients with investigational drugs including 2-iminobiotin (a selective neuronal and inducible nitric oxide synthase inhibitor), steroid (an adrenal cortex hormone and also a suppressor of inflammation), tocilizumab (an interleukin-6 receptor antibody and modulates systemic inflammatory response), and vasopressin (a vasopressor) in the Netherlands, Denmark, and Korea (NCT02836340, NCT04624776, NCT03863015, NCT03191240) [32]. This trial investigates Neu2000K, a first-in-class multi-target neuroprotectant that moderately and selectively blocks the NR2B subtype of NMDA receptor and also functions as a potent reactive oxygen species scavenger. The AWAKE trial will provide valuable safety and efficacy data that documents the neuroprotective properties of Neu2000K in OHCA and provides a broader implementation and a more extensive phase III clinical trial.

### Trial status

This report describes the study protocol version 1.3 as of December 20, 2017. The first patient was randomized on November 29, 2018. As of May 15, 2022, 89 patients were recruited for this study. AWAKE is currently recruiting study patients at all participating centers.

## Data Availability

The study data can be supplied on a reasonable request and with approval from relevant authorities.

## Abbreviations

AWAKE: Antioxidant and NMDA receptor blocker Weans Anoxic brain damage of KorEa OHCA patients
CPC: Cerebral performance category
ECMO: Extracorporeal membranous oxygenation
NMDA: *N*-Methyl-d-aspartate
mRS: Modified Rankin Scale
OHCA: Out-of-hospital cardiac arrest
ROSC: Return of spontaneous circulation
